#### Primary outcome

The effect of bezafibrate on itch will be confirmed by a Fisher’s exact test on the difference in the proportion of patients responding to treatment (≥50% reduction of itch intensity in the VAS score at day 21 compared to day 0) between the bezafibrate and the placebo groups.

#### Secondary outcomes

In exploratory analyses, we will test:The absolute effect of a 3-week treatment as well as a 2-week follow-up on VAS and 5D Pruritus Scale scores (day 0 versus day 21 and day 21 versus day 35) as well as the difference of these effects between both groups (unpaired *t* tests)The effect of a 3-week treatment on daily morning and evening VAS scores in both groups separately (repeated measures analysis of variance (ANOVA) days 1–21)The difference in time at which patients reach the primary endpoint (50% reduction in itch intensity) for the first time between both groups (unpaired *t* test)The difference in morning and evening VAS scores within patients at day 1 (irrespective of treatment group, paired *t* test)The difference in the effect of a 3-week treatment as well as a 2-week follow-up on LDSI2.0 questionnaire total and subdomain scores between both groups (day 0 versus day 21 and day 21 versus day 35, unpaired *t* test)The difference in the effect of a 3-week treatment as well as a 2-week follow-up on serum ATX activity, AST, ALT, ALP, γGT, bilirubin, albumin, creatinine, CK, LDH, glucose, total cholesterol, HDL- and LDL-cholesterol and triglycerides between both groups (day 0 versus day 21 and day 21 versus day 35). Depending on the distribution of the data, parametric or nonparametric tests will be chosen, i.e., unpaired *t* test and Mann-Whitney *U* test, respectivelyThe number of AEs and SAEs during and after treatment will be listed in a table. As few AEs are expected, no statistical analysis will be applicable to compare between groups

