### Sample size calculation

We will compare the proportion of patients from both treatment arms who show a clinically relevant response to treatment which is defined as a reduction in itch intensity of at least 50%. Based on former placebo-controlled trials for cholestatic itch, selecting data only from patients with itch scores of 5 or higher at baseline who were treated for at least 2 weeks, we estimated that 18% of placebo-treated patients will show the defined response [30, 35, 49–51]. Based on empiric observations we believe that at least 50% of bezafibrate-treated patients will respond. Thus, we anticipate a difference in proportions between the bezafibrate and placebo groups of 32%.

Using Fisher’s exact test with alpha set at 0.05 we need 38 patients per group for a power of 0.80 for two-sided testing. Taking into account a 10% possible dropout we will include 84 patients (42 per arm) in this study. This power calculation was made after consulting a statistician and using the statistical program nQuery Advisor version 3.0.

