### Recruitment

Patients are recruited from outpatient clinics of participating academic medical centers. After informed consent, based on oral and written information (see Additional file 1) provided by study physician or nurse, patients are enrolled at day 0 if the itch intensity is at least 5 out of 10 on a VAS, and all other inclusion and exclusion criteria are met. For all patients who drop out before day 21, we will include a replacement, whereas patients dropping out during the follow-up phase will not be substituted (see also Additional file 3).

The first participant was enrolled in April 2016. Recruitment is expected to be completed in 18 months, and will be enhanced by creating awareness among clinicians through regular presentation of the trial at (inter)departmental meetings. Moreover, we keep close contact with patient organizations to advertise the trial.

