### Randomization and blinding

After informed consent, patients will be allocated randomly to either bezafibrate or placebo treatment (ratio 1:1) as per a computer-generated randomization schedule with randomly varying block sizes (maximum block size of 4) by the sites’ investigator through a web-based module written in ALEA (https://nl.tenalea.net, copyright NKI AVL, Amsterdam) by the AMC Clinical Research Unit. Stratification takes place for the VAS itch score at day 0 (2 strata: 5 cm ≤ VAS < 7.5 cm versus 7.5 cm ≤ VAS ≤ 10 cm). An automated email with the resulting randomization number will be sent to the trial pharmacy which allocates the patient to one of the two treatment arms and distributes the study medication accordingly to the patients, using identical packaging for placebo and bezafibrate tablets. This way, patients, physicians and outcome assessors stay blinded for treatment allocation. All investigators are aware that the pharmacy keeps the randomization list locked until all patients have completed the study, and that a request for unblinding can only be done in case a serious adverse event (SAE) occurs. Investigators at all sites keep their own subject identification log, in a secure place, and handle all personal data according to the local regulations on personal data protection.

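### The exploratory day 0 to day 21 group comparisons use unadjusted tests on change; adjusting for the day-0 value would gain precision at almost no cost (minor)

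*Protocol article*

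**What the plan says.** The Secondary outcomes section of the protocol article names the between-group tests itself.

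- VAS and 5D: the effects over day 0 to 21 and day 21 to 35, "as well as the difference of these effects between both groups (unpaired" *t* tests).
- LDSI2.0: the difference in effect on "LDSI2.0 questionnaire total and subdomain scores between both groups (day 0 versus day 21 and day 21 versus day 35, unpaired" *t* test).
- Autotaxin activity and laboratory values: the same two periods, compared by unpaired *t* test or Mann-Whitney *U* test according to the distribution.

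None of these entries has a baseline or stratum term. Under Randomization and blinding, "Stratification takes place for the VAS itch score at day 0", in two bands split at 7.5 cm. VAS, 5D and LDSI2.0 are scored at all three visits (Discussion), and serum is drawn at days 0, 21 and 35 (Biological specimens).

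Associative analyses foresees multivariable work, where applicable, to see which factors relate to treatment outcome. It lists the itch stratum but no baseline 5D, LDSI2.0, autotaxin or laboratory value. Both Secondary outcomes and the Discussion describe everything beyond the primary endpoint as exploratory.

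**The concern.** A change score subtracts the whole day-0 value, which amounts to fixing the regression slope of follow-up on baseline at 1. When the true slope is smaller, this over-corrects: the difference between arms carries extra noise, and an arm that starts higher by chance appears to improve more through regression to the mean. A model that estimates the slope avoids both effects.

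With about 40 patients per arm, chance imbalance is not negligible. Stratification limits it for VAS only, and the planned VAS test ignores the stratum. What is at stake is the width of the intervals, and the trustworthiness of single estimates, for the quality-of-life, cholestasis and autotaxin questions that the article sets as secondary objectives. Nothing else in the article supplies a baseline-adjusted effect for them.

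**Working it through.** **The plan's own figure.** The article states: "Using Fisher’s exact test with alpha set at 0.05 we need 38 patients per group for a power of 0.80 for two-sided testing". The inputs are 18% ("we estimated that 18% of placebo-treated patients will show the defined response") and 50% ("we believe that at least 50% of bezafibrate-treated patients will respond"). Exact enumeration gives Fisher power 0.785 at 37 and 0.800 at 38 per arm, so 38 reproduces. It is used below as the evaluable number per arm; the figure concerns the primary endpoint and is not in question here.

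**Inputs for the comparison.** The article gives no SD or baseline-to-follow-up correlation for any secondary outcome. Everything below rests on an assumed correlation r, day-0 SD s0 and day-21 SD s1, the same in both arms.

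**Formulas (large sample).**

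- Change score: variance proportional to s0² + s1² − 2·r·s0·s1
- Baseline-adjusted (ANCOVA): variance proportional to s1²·(1 − r²)
- With s0 = s1, the ratio adjusted/change is (1 − r²)/[2(1 − r)] = (1 + r)/2

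**Equal SDs, 38 per arm.** The last column is the power of the adjusted analysis for an effect that the change-score test detects with 80% power (normal approximation).

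| r | Variance ratio | CI narrower by | Equivalent n per arm (38/ratio) | Power |
|---|---|---|---|---|
| 0.2 | 0.60 | 22.5% | 63 | 95% |
| 0.5 | 0.75 | 13.4% | 51 | 90% |
| 0.7 | 0.85 | 7.8% | 45 | 86% |
| 0.9 | 0.95 | 2.5% | 40 | 82% |

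**VAS with baseline restricted to 5–10 cm.** Assume s0 = 1.4 (a uniform spread over that range would have SD 5/√12 = 1.44).

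- s1 = 2.0, r = 0.2: 3.84/4.84 = 0.79
- s1 = 2.0, r = 0.5: 3.00/3.16 = 0.95
- s1 = 2.8, r = 0.2: 7.53/8.23 = 0.91
- s1 = 2.8, r = 0.5: 5.88/5.88 = 1.00

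In the last case the slope r·s1/s0 equals 1 and nothing is gained. Over these scenarios the interval is 0 to 11% narrower (1 − √0.79 = 0.11).

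**Chance imbalance.** Under simple randomisation the SE of the day-0 difference is √(2/38) = 0.23 SD, with a 95% range of about ±0.45 SD. With equal SDs, an imbalance of 1 unit moves the change-score difference by −(1 − r). A 4,000-run simulation with no true effect gave −0.72, −0.51 and −0.30 at r = 0.3, 0.5 and 0.7, against about 0 for ANCOVA. At r = 0.5, an imbalance of 0.45 SD therefore shifts the estimate by about 0.5 × 0.45 = 0.22 SD. Averaged over all runs, both estimators were at zero.

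**Day 21 to 35.** Take a model with days 21 and 35 as outcomes, treatment by visit, and the day-0 value and stratum as covariates with one coefficient across visits. Those covariates cancel from the day-35 minus day-21 difference. With complete data, the contrast is the difference in mean change that the plan already tests. In three simulated complete data sets of 38 per arm, estimates and SEs agreed exactly (for example 1.852, SE 0.306, both ways).

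**The case against.** The strongest reply is that a change-score comparison of randomised groups is a legitimate analysis, and that the article declares these analyses exploratory behind a single confirmatory endpoint. Both statements are correct. A reader might infer that the planned tests are biased or invalid; they are not. The imbalance effect is error conditional on the baseline actually drawn, not bias on average.

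Three further inferences also go too far.

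- *The day 21 to 35 test is flawed because it starts from a post-randomisation value, or because it drops patients.* It is a contrast of randomised groups and, as shown, the same quantity that an adjusted model would estimate. The statement that "patients dropping out during the follow-up phase will not be substituted" concerns replacing recruits, not excluding data. The Statistical analysis plan section leaves room for imputation or model-based handling of missing values.
- *One extreme baseline can drive a skewed laboratory result.* The plan offers Mann-Whitney *U* for such data, which bounds the influence of a single value. That test is still unadjusted.
- *Adjustment saves 25–40% of variance.* That holds only for equal SDs and r between 0.2 and 0.5. Higher correlations, plausible for laboratory values over three weeks, shrink the gain, and the VAS scenarios give less.

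What the reply does not provide is a reason to prefer the unadjusted comparison for day 0 to 21. Nor can the point be left to an unseen analysis plan, because the article itself fixes the tests.

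**Conclusion.** The point holds as a minor efficiency improvement, confined to the exploratory day 0 to day 21 comparisons. Under the assumed values, the adjusted variance is 0.60 to 0.95 of the change-score variance for equal SDs and r from 0.2 to 0.9, and about 0.79 to 1.00 for VAS. These are large-sample ratios for the *t*-test comparisons. Where the slope is near 1, the degree of freedom spent on the covariate makes adjustment trivially worse. No ratio was computed for outcomes that would go to Mann-Whitney *U*.

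No confirmatory conclusion depends on this. The primary Fisher test and the sample size are untouched.

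**What to change.** For each continuous secondary outcome, replace the unpaired test on day 0 to 21 change with an ANCOVA of the day-21 value on treatment, the day-0 value of that outcome and the VAS stratum. Analyse skewed laboratory values and autotaxin on the log scale, so that the effect is a ratio of geometric means. Report the adjusted difference or ratio with its 95% CI.

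A mixed model with days 21 and 35 as outcomes, treatment by visit and the same covariates is an equivalent route. The day 21 to 35 comparison may stay as planned; there, the mixed model helps only by using patients who miss one of the two visits.

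The cost is a few lines of analysis wording, settled before unblinding. No new data, visits or patients are needed.

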### Aim of this study: to evaluate the antipruritic effect of fibrates

The itch-relieving effect in the abovementioned studies was not measured as a primary outcome and was thus not systemically objectified by current quantification methods for itch intensity such as the widely used Visual Analog Scale (VAS) (validated in [33], discussed in [34]). Moreover, antipruritic effects were not controlled for while a considerable placebo effect should be taken into account (about 30% itch reduction was seen upon placebo treatment in one study [35]). Thus, we would like to validate the promising effect of fibrates on itch as a primary outcome in a double-blind, randomized placebo-controlled study.

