### Outcomes

#### Visual Analog Scale (VAS) itch score

The primary endpoint will be calculated from VAS scores obtained at study visits 1 and 2 (at start and stop of therapy), asking patients to report the maximum itch intensity of the past 24 h. We are using VAS itch scores as it is the most widely used method to assess itch intensity [33]. The scale consists of a 10-cm horizontal line divided into ten equal parts numbered 0 to 10. The 0 on the left is accompanied by a smiling face and the text “no itch at all,” the 10 on the right is accompanied by a sad-looking face and the text “worst itch possible.” Mostly to promote treatment fidelity, during the 21-day treatment period, patients will be asked to keep a diary to score their itch intensity (VAS) twice daily (after waking up in the morning and before going to bed in the evening) and make notes such as the use of co-medication, side effects and other information.

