Although we are capturing itch intensity data using various measures in parallel (VAS, 5D and LDSI2.0 itch scores during the three visits as well as daily morning and evening VAS scores from the diaries), we endeavor to avoid the statistical multiplicity problem by having defined a single confirmatory primary endpoint, based on VAS scores during the study visits. All other data will be used in exploratory analyses only, as defined in the protocol. For example, previous studies described diurnal variation of itch intensity [2, 52] where most patients reported more intense itch in the late evening and early nighttime. By using diaries, we will also acquire information on how fast a possible effect occurs. In addition, we hope that the use of a diary stimulates compliance and increases accuracy of co-medication usage and reports of side effects.

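### The daily diary VAS course is tested only within each arm, so the analysis labelled as the effect of treatment cannot separate bezafibrate from placebo

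*Protocol article*

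**What the plan says.** The outcomes section (Visual Analog Scale itch score) states that "patients will be asked to keep a diary to score their itch intensity (VAS) twice daily", morning and evening. It gives the main purpose as "Mostly to promote treatment fidelity, during the 21-day treatment period". That yields up to 2 × 21 = 42 scores per patient.

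Secondary outcomes, in a list introduced as exploratory, fixes the analysis of these scores. The item reads "The effect of a 3-week treatment on daily morning and evening VAS scores in both groups separately", and the method given for it is "repeated measures analysis of variance (ANOVA) days 1–21".

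The neighbouring items are worded differently. The visit-score item covers "The absolute effect of a 3-week treatment as well as a 2-week follow-up on VAS and 5D Pruritus Scale scores" and then adds the difference of these effects between the groups. The LDSI2.0 and laboratory items also name a between-group test. The item directly after the diary ANOVA compares, between arms, the time at which patients first reach a 50% reduction.

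Three other places bear on the point:

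- The aim section warns that "about 30% itch reduction was seen upon placebo treatment in one study" and gives this as a reason for a placebo-controlled design.
- The Discussion says "By using diaries, we will also acquire information on how fast a possible effect occurs", and makes everything other than the visit-based primary endpoint exploratory.
- The statistical analysis plan section leaves missing data to imputation or to suitable models, sets P < 0.05 as the significance threshold, and announces a table of percentage change per group with P values.

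**The concern.** A repeated-measures ANOVA run inside one arm asks whether mean itch changes over the 21 days in that arm. It does not ask whether the change differs from placebo. Placebo response, natural fluctuation and regression to the mean after selection on a VAS of at least 5 cm can all produce a fall in either arm. A significant time effect under bezafibrate is thus expected to some degree even if the drug does nothing.

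Two separate tests also invite the reader to set one P value against the other. Significant in one arm and not significant in the other is not a test of the difference between arms, and its false-positive rate is not controlled.

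At stake is the mean day-by-day course of itch, the richest description of response in the trial. As written, it would be reported as an effect of treatment without using the randomisation. The article faults earlier fibrate studies for just this lack of control.

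**Working it through.** **The plan's own figure.** The article gives no figure for the diary analysis. The calculations use its number per arm: 38 evaluable, 42 randomised. The 38 reproduces: exact power of the two-sided Fisher test at 18% versus 50% and alpha 0.05 is 0.800 with 38 per group and 0.785 with 37.

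**Step 1: is there a between-arm test of the daily course?**

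| Item in Secondary outcomes | Data | Between-arm test named |
|---|---|---|
| Visit VAS and 5D, days 0, 21, 35 | visits | yes |
| Daily morning and evening VAS, days 1–21 | diary | **no, each group on its own** |
| Time to first 50% reduction | must be diary, as visits fall only on days 0, 21 and 35 | yes |
| Morning versus evening VAS, day 1 | diary | no, treatment ignored by design |
| LDSI2.0; laboratory values | visits | yes |

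The diary is compared between arms once, for time to a threshold. Mean daily itch is not.

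**Step 2: what can separate tests show if the drug does nothing?**

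From the article: 38 per arm; 21 daily scores; two-sided 0.05; placebo fall about 30%. Assumed, because the article gives no values: start at 7 cm, linear fall, SD 2 cm, first-order autoregressive correlation 0.8 or 0.9. The 30% figure corresponds to 0.30 × 7 = 2.1 cm. It comes from one study, so smaller falls of 1.0 and 1.5 cm were run as well.

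Both arms had the same true course; 2000 trials per setting; *k* = 21 days, *n* = 38; degrees of freedom Greenhouse–Geisser corrected.

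- Within one arm: F = [n Σ(ȳ_t − ȳ)² / (k − 1)] / [residual SS / ((k − 1)(n − 1))].
- Group-by-time, with d_t the difference in arm means on day t: F = [(n/2) Σ(d_t − d̄)² / (k − 1)] / [pooled residual SS / ((k − 1)(2n − 2))].

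| True fall in both arms | Placebo arm significant | Exactly one arm significant | Group-by-time significant |
|---|---|---|---|
| 1.0 cm | 44–52% | 49–50% | 5.1–5.4% |
| 1.5 cm | 78–84% | 29–34% | 5.0–5.8% |
| 2.1 cm | 98–99% | 2–4% | 4.4–5.5% |

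Ranges run over the two correlations. Arithmetic check: for independent arms, the chance that exactly one is significant is p₁(1 − p₂) + p₂(1 − p₁). At 1.0 cm and correlation 0.8 this is 0.443 × 0.558 + 0.442 × 0.557 = 0.493, against 0.486 simulated.

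The two misreadings trade off. With a large common fall, both arms are significant and the bezafibrate result tells nothing. With a moderate fall, discordant results are common and look like a drug effect. The group-by-time test stays near 5% throughout.

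**Step 3: missed entries, a conditional risk.** Classical repeated-measures ANOVA needs a complete series. If nothing is imputed and entries are missed independently with probability m (assumed; the article gives no rate), the expected number of complete patients out of 42 for one 21-day series is 42 × (1 − m)^21:

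- m = 1%: 42 × 0.810 = 34.0
- m = 2%: 42 × 0.654 = 27.5
- m = 5%: 42 × 0.341 = 14.3
- m = 10%: 42 × 0.109 = 4.6

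**The case against.** The strongest reply is that little hangs on this item. The list is exploratory, there is a single confirmatory endpoint based on visit scores, and the diary is kept mainly to support adherence. Drug is compared with placebo for the primary endpoint and for visit VAS, 5D, LDSI2.0 and laboratory values. All of this stands, and it limits the weight of the point. It does not make a within-arm test answer a between-arm question.

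Three stronger readings are tempting, and the documents do not support them.

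- *The diary yields no drug-versus-placebo comparison at all.* It yields one: time to first 50% reduction is compared between arms and can only come from the diary. The speed of response therefore has a randomised comparison. But that item concerns the crossing of a threshold, and a patient who never crosses it has no time to enter. It does not compare mean daily itch.
- *One missed entry removes a patient.* The article does not say so. This is a default of the classical method, and the statistical analysis plan section allows imputation or other models. Nor can it be said that most patients would be lost: at an assumed 1% or 2% missing, about 34 or 27 of 42 remain.
- *The placebo arm is almost certain to be significant.* Under the assumptions used, this holds only for a fall of about 2 cm. At 1.0 cm it is about an even chance.

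The visit-score item also mentions an absolute effect, but it names a between-arm test and needs no change on this account.

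It is also fair to say that a mixed model over 21 days is not free of choices: an unstructured covariance has 21 × 22 / 2 = 231 parameters for 76 to 84 patients. This is an argument for specifying a simpler structure, not for keeping separate ANOVAs.

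**Conclusion.** The point holds in a limited form. The protocol article fixes the analysis of the daily itch course as a test within each arm and presents the result as the effect of treatment. Given the placebo response that the article itself expects, neither a within-arm time effect nor a contrast of two within-arm P values can be credited to bezafibrate. The mean daily course has no randomised comparison.

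That the test cannot separate drug from placebo follows from the wording alone and needs no assumption. The simulated sizes (one arm significant and the other not in 49–50% or 29–34% of trials without any drug effect, at common falls of 1.0 or 1.5 cm) depend on the assumed SD, correlation and linear course. The loss of patients through missed entries depends on an assumed missing rate and on nothing being imputed.

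The primary endpoint, its test and its sample size are not affected. This is a change worth making before unblinding to an exploratory analysis, not a threat to the trial's main conclusion.

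**What to change.** Replace the separate ANOVAs by one linear mixed model on all available diary scores from both arms, fitted separately for morning and evening or jointly. Include treatment, day, treatment-by-day and the day-0 VAS. Pre-specify a parsimonious within-patient covariance, for example first-order autoregressive with a patient random effect, or model weekly means instead of 21 days. Report the between-arm difference with a 95% CI for the whole period and by week. Show the within-arm curves as description, without P values.

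The model uses incomplete diaries without deleting patients, provided that entries are missing at random given the scores observed.

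The cost is a change of wording and somewhat more modelling work, including the choice of covariance structure, which should be settled before unblinding. No new data or patients are needed, and SPSS, the package the article names, can fit the model.

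### An unpaired t test is named for time to first 50% itch reduction, although many patients, unequally by arm, will be right-censored at day 21

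*Protocol article*

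**What the plan says.** The Secondary outcomes section of the protocol article introduces its list as exploratory. One item is "The difference in time at which patients reach the primary endpoint (50% reduction in itch intensity) for the first time between both groups (unpaired" *t* test).

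Other sections bear on it:

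- **Sample size calculation.** For placebo, "we estimated that 18% of placebo-treated patients will show the defined response"; for the active arm, "we believe that at least 50% of bezafibrate-treated patients will respond". The Primary outcome section fixes this response at day 21 against day 0.
- **Visual Analog Scale (VAS) itch score.** The diary is scored twice a day during the 21 days of treatment, so at most 42 diary scores exist per patient and none is scheduled after day 21.
- **Statistical analysis plan.** Analyses follow the intention-to-treat principle. Missing data are covered only in general terms (imputation or specific models), with details to come in the results paper.
- **Discussion.** The diaries are also meant to show how quickly an effect sets in.

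No section says how a patient who does not reach the reduction enters the t test, and no censored-data method is named.

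**The concern.** A t test needs a time for every patient. A patient who has not reached the reduction when the diary ends is known only to have a time beyond day 21. That is right-censoring, not a missing value, so the general missing-data wording does not cover it. The planned response rates also make censoring unequal between the arms.

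Two ways of forcing such data into a t test are open, and each has a defect:

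- **Leave out patients without a time.** The comparison is then between subsets defined by an outcome after randomisation. It asks whether responders on one arm respond earlier than responders on the other, and it ignores that more patients respond on one arm.
- **Enter day 21 for them.** Everyone is kept, but a lower bound is treated as an observed time.

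At stake is the between-arm comparison of speed of onset, one of the uses the article gives for the diary. The confirmatory result is not at stake.

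**Working it through.** **1. The plan's own figure.** Inputs from the Sample size calculation: 18% and 50%, Fisher's exact test, two-sided alpha 0.05. Full enumeration gives power 0.785 at 37 per group and 0.8004 at 38, so the stated 38 is reproduced. With 42 per arm and 10% dropout, 42 × 0.90 = 37.8, about 38.

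**2. Patients without a time, on those rates.**

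- Placebo: 42 × 0.18 = 7.6 responders, 34.4 non-responders (82%).
- Bezafibrate: 42 × 0.50 = 21 responders, 21 non-responders (50%; fewer if response exceeds 50%).
- Together: 28.6 responders and 55.4 non-responders of 84 (66%).

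These are day-21 rates. The article gives no rate for ever having reached the reduction by day 21, which will be higher if some patients reach it and lose it. If ever-reached rates were 1.47 times the day-21 rates (26% and 74%), the share never reaching it would be 50% overall; at 2 times (36% and 100%), 32%. So 82% and 50% are upper figures.

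**3. Model for the size (assumption).** Constant hazards chosen so that 18% and 50% reach the event by day 21: λ = −ln(1 − p)/21.

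- Placebo: 0.1985/21 = 0.00945 per day. Bezafibrate: 0.6931/21 = 0.0330 per day. Hazard ratio 3.5.
- Mean time among reachers = 1/λ − 21(1 − p)/p. Placebo: 105.82 − 95.67 = 10.15 days. Bezafibrate: 30.30 − 21.00 = 9.30 days.

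A 3.5-fold hazard ratio thus shrinks to under one day's difference among reachers, on about 8 and 21 patients.

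**4. Simulated power.** 42 per arm, half-day grid, no dropout, unstratified log-rank test, 4,000 trials per row. Rows 2 to 4 assume more patients reach the reduction.

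| Reach 50% by day 21, placebo / bezafibrate | Hazard ratio | t test, reachers only | t test, others set to day 21 | Log-rank |
|---|---|---|---|---|
| 18% / 50% | 3.5 | 7% | 80% | 88% |
| 30% / 65% | 2.9 | 9% | 86% | 92% |
| 40% / 75% | 2.7 | 13% | 89% | 93% |
| 50% / 80% | 2.3 | 15% | 82% | 87% |

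Repeated runs of the first row gave 6% to 7%, 80% to 82% and 88% to 89%. As a check, Schoenfeld's formula needs 21 events for 80% power at this hazard ratio; the 28.6 expected give about 92%.

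**5. What the reachers-only test responds to.** If the timing among reachers is the same in both arms (assumed mean 9 days, SD 5), it rejects in about 5% of trials although 50% against 18% reach the event. That is its nominal error rate: it does not see the difference in how many patients reach the reduction.

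**The case against.** The strongest reply is that the article nowhere says that patients without an event are dropped. With day 21 entered for them, the t test loses only about eight points of power to the log-rank test. If every diary ran to day 21, that version could even be read as comparing mean event-free time within 21 days. This stands as far as it goes, so the near-total loss of power belongs to one handling and not to the named test as such. But the article does not specify that handling, it would answer a different question from the one written down, and it gives no value to patients who leave before day 21, for whom the plan allows 10%.

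The analysis is also exploratory, and the article says that the diary serves mostly to support adherence. That limits the severity. It does not make the test suitable, and because the method is named, this is not a detail left to a fuller document.

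A reader might infer more than the documents support:

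- **That most patients will never reach the reduction.** This reads day-21 rates as ever-reached rates. In the bezafibrate arm the plan implies at most half even at day 21. The point does not need a majority.
- **That the test will mislead on direction.** In the constant-hazard model the bezafibrate mean among reachers is later in about 37% of trials, but this is mostly noise; a significant result in the wrong direction occurs in about 1.4%. Much larger figures (43% with assumed means of 10 and 6 days, SD 5) rest on timings found nowhere in the article.
- **That a single low diary score will count as response.** The primary score is taken by "asking patients to report the maximum itch intensity of the past 24 h", the diary is scored morning and evening, and the Discussion cites earlier studies "where most patients reported more intense itch in the late evening and early nighttime". But the article does not say which baseline or diary score defines this event, and an article may leave that to the full protocol. A chance-crossing probability of 6% to 62% for an unimproved patient assumes a mean, a spread and independent readings that the article does not give.

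**Conclusion.** The point holds. The article names an unpaired t test for a time that is right-censored at day 21, with up to about 82% of placebo and up to about 50% of bezafibrate patients censored on the planned day-21 rates. The test as written has no rule for these patients. Dropping them breaks the intention-to-treat principle and leaves about 7% power; setting them to day 21 gives about 81% but treats censored times as observed; the log-rank test gives about 89%.

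The power figures assume constant hazards, 42 patients per arm and no dropout. The ordering holds in the scenarios with higher ever-reached rates, where the reachers-only test has 9% to 15% power and the log-rank test 87% to 93%. It would be wrong to conclude that the t test has almost no ability to detect a difference in speed of onset, since that is true only if non-reachers are dropped. The primary Fisher test and the sample size are unaffected, so this is a correction worth making and not a threat to the trial's main conclusion.

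**What to change.** In the list of secondary analyses, replace the unpaired t test for this item with Kaplan-Meier curves by arm and a log-rank test (or Cox model with hazard ratio and confidence interval), stratified by the two VAS strata used at randomisation. Include all randomised patients, also those who drop out before day 21 and are replaced. Censor patients who have not reached the reduction at day 21 or at their last diary entry, whichever is earlier.

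The cost is a change of wording in the analysis plan, best made before unblinding. It needs no new data, visits or patients.
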